**Problem**

Improving maternal health and reducing maternal mortality are priorities in public health, highlighted as one of the eight Development Goals of the Millennium. Considering that the highest proportion of maternal deaths occur during the period of childbirth, it is necessary to generate strategies for the uptake and knowledge transfer (KT) in health focused on the effective communication of basic and relevant information in maternal and neonatal health to reach the general population. Knowledge transfer strategies, such as education, reminders and knowledge capsules, have been described as ways to ensure the use of scientific evidence by health professionals and decision makers to benefit patient health. However, little has been done regarding patients and the community, with strategies that facilitate the empowerment of patients and the community on the topic of health care, specifically regarding pregnant women and children, and how this could improve results related to maternal health. In light of the above, this research intends to answer the following questions: (1) What are the characteristics and relevant content in the design of strategies of social appropriation of knowledge in maternal and neonatal security aimed at patients and the community? (2) What is the effectiveness of 12 knowledge capsules in maternal and neonatal health to achieve the social appropriation of this knowledge in the target population?

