In light of the above, this research intends to answer the questions: (1) What are the characteristics and relevant content in the design of strategies of social appropriation of knowledge in maternal and neonatal security directed to patients and to the community? and (2) What is the effectiveness of 12 knowledge capsules in maternal and neonatal health to achieve social appropriation of this knowledge in the target population?

1. **Justification**

In Colombia, the figures of maternal mortality reported by the Ministry of Health and Social Protection (MSPS), exceed the national targets established in 2003 in the emergency plan against maternal mortality [4]. In 2011, the Health Situation Analysis Report 2013 [13] described an MMR of 68.82 deaths per 100,000 live births; in addition it is reported that maternal mortality in the department of Chocó is 4.2 times higher than the national average, showing the highest number of maternal deaths in the country, with an MMR of 357.97 deaths per 100,000 live births, followed by the Guajira department, with an MMR of 166.85 per 100,000 live births. This statistic, in turn, was shown to be higher in the population located in the poorest quintile, being 1.72 times higher in the departments of the quintile with a greater proportion of Unsatisfied Basic Needs (Vaupés, Sucre, Córdoba, Guainía, La Guajira, Vichada, and Chocó).

Payers, insurers and regulatory bodies increasingly expect the integration of new knowledge with health professionals and scientific evidence in daily practice [1, 2]. This is based on the objectives of the use of evidence-based practice [10], which has shown that it has a direct impact on improving patient outcomes [10].

The KT's interactive models emphasize the nature of the person in the process. That is to say, the transfer is made easier when the producers of the knowledge and the users of it understand each other and are both familiar with the needs, objectives and preferences. Although the importance of familiarity has been documented, it is often weak. Researchers often express frustration with the difficulty of understanding the internal workings in the user groups they evaluate [14].

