The objective of research in KT is to develop theoretical bases to optimize knowledge. The field of research in KT is growing, but still presents methodological and conceptual challenges. The interventions in KT generally have a complex design, with equally complex evaluations [11].

International organizations have implemented strategies aimed at health institutions and professionals, with tools such as evidence-based clinical practice guidelines, institutional management protocols and the safe delivery checklist, with the purpose of reducing variability in clinical practice and improving the quality of delivery care. Likewise, strategies for the standardization of clinical practices in health have been developed, such as clinical practice guidelines in versions for patients and programs that highlight the importance of early prenatal control and preparation for childbirth. These guides seek to emphasize the use of existing evidence and theory throughout the process of childbirth. In addition, research based on KT theory provides benefits such as the development of a generalized framework to measure barriers, facilitators and optimization of the selection of the components of the interventions, as well as the design of a strategy for evaluating them [11].

An informed and empowered patient has even been shown to improve patient safety and constitutes a safety barrier in the presence of adverse events [41].

Considering the findings described above, and in view of the high figures of maternal deaths that still occur in our environment, in 2010 the WHO created the “Making Pregnancy Safer” (MPS) department. This department states that in order to reduce maternal mortality, not only the improvement of health services is required, but also collective participation, which contributes to the empowerment of women, families and communities to improve and increase the control of maternal and neonatal health, as well as to increase access to quality health services [42].

This project therefore intends to develop knowledge capsules in maternal and neonatal health based on the theory of KT and to evaluate its potential effectiveness in order to achieve social appropriation of knowledge, based on neuromarketing tools.

1. **Objectives**
   1. **Overall objective**

Design and evaluate the effectiveness of 12 knowledge capsules in maternal and neonatal health through a pilot study to generate knowledge appropriation in the target population.

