Based on the results of the systematic review of strategies for the transfer and social appropriation of knowledge, on the results of formal consensus of experts, and on the theoretical foundations of neurocognition and neuromarketing, the design of health knowledge capsules will be developed together with experts in health psychology, promotion and prevention in health, as well as experts in diagramming and development of audiovisual products. During this phase the final scripts, the graphic outline of the clips, their duration, the soundtrack and the production will be created, based on the results of the previous phases.

1. **Phase 5. Evaluation of effectiveness of knowledge capsules in terms of social appropriation of knowledge.**

A neuromarketing strategy will be applied in the Cognitive Neuroscience and Communication Laboratory of the National University of Colombia, with the objective of evaluating the effectiveness of the knowledge capsules in maternal and neonatal health in terms of social appropriation of knowledge, using measurements of attention, emotional response and remembrance.

The analysis will be conducted to find differences between subgroups or categories of educational level, defined as follows:

0 = No study

1 = Primary or Baccalaureate (basic education or secondary education)

2 = Higher Education (undergraduate and postgraduate)

*- Design:* Cross-over experimental study in which a group of pregnant women, non-pregnant women and adult men will be exposed to 13 clips, 12 of which will be produced through this knowledge transfer strategy and one will be an unrelated standard video that will be used as a control. The order of viewing the videos will be assigned randomly for each subject, so that each subject will have 13 evaluations. The random allocation tables will be generated by computer, and one will be made for each educational stratum (without education, with primary or secondary education, and with post-secondary education) and group (pregnant woman, non-pregnant woman and man). It is expected to have a minimum sample of 150 subjects.

*- Population and sample:*

- Inclusion criteria:

Pregnant women, non-pregnant women and men over 18 years of age, who agree to participate in the study through informed consent.

- Exclusion criteria:

participants who presented serious health problems linked to pregnancy or who presented any clinically significant visual and auditory problems, which affected the viewing of the videos.

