*- Type of sampling:* not probabilistic, for convenience.

*- Sample size:*

Using the statistical analysis program for biomedical, social and behavioral sciences G * Power 3, the sample size was calculated for a one-way analysis of variance (ANOVA) design and fixed effects, using the F statistic. The selection of the parameters was made for the recall outcome, expecting that the differences of the capsules compared with the video control would be moderate. The parameters were therefore defined as follows: moderate effect size f = 0.3; power (1-β) = 0.90 and alpha (α) = 0.05 for three groups. The calculation yielded a result of 144 for the total sample. Considering that there would be no follow-up of the participants and the measurements would be taken in a single session, a low number of losses was estimated (mainly due to failures in the registry), so a minimum of 150 subjects was defined as a total sample, 50 for each group.

*Process:*

All participants will sign an informed consent (Annex 1) after explaining the objectives of the study and procedures that will be carried out. Participation will be completely voluntary.

The procedure consists of the projection of 12 health knowledge capsules of approximately 35 seconds each, and a control clip, not related to the subject. The control clip will be a standard video, which provides information on reproductive health and maternal safety, but which has not been designed based on evidence or following strategies based on neuromarketing.

The observation of the videos will be free; that is, they will not be explained to the participants during the screening, or the content of them. All the videos will be seen by the participants, but the observation of each one will be assigned in a random way.

The successive order of visualization of the videos is presented in Figure 1. It shows the successive ordering of the clips. However, the actual order of visualization of the clips will be done randomly for each of the subjects.

[figure not shown]

***Figure 1.*** *Form in which the assignment and evaluation of the effect of each intervention is planned.*

The process of consolidating results will be done for each clip as shown in Figure 2.

***Figure 2.*** *Selected sample, and methodological format of analysis of the clips*

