***Statistic analysis:***

Hypotheses raised:

- **Study hypothesis 1**

Comparison between capsules and video control

H0: μ capsule X = μ video control

Ha = μ capsule X ≠ μ video control

*μ = average attention, emotional reaction and recall*

- **Study hypothesis 2**

Comparison between groups: men, non-pregnant women, pregnant women

H0: μ1 = μ2 = μ3

Ha: ∃μj ≠ μ j = 1, 2, 3

*μ = average attention, emotional reaction and recall*

- **Study hypothesis 3**

Comparison between levels of schooling: none, primary, baccalaureate, undergraduate, postgraduate

H0: μ1 = μ2 = μ3

Ha: ∃μj ≠ μ j = 1, 2, 3, 4, 5

*μ = average attention, emotional reaction and recall*

- **Study hypothesis 4**

Comparison between family history: children, no children

H0: μ1 = μ2

Ha: μ1 ≠ μ2

*μ = average attention, emotional reaction and recall*

A descriptive analysis of the measured variables will be carried out. The qualitative variables will be described in proportions, and calculations for averages and standard deviation that follow a normal distribution will be performed for quantitative variables. For variables that do not follow this distribution, medians and interquartile ranges will be calculated. The normality of the variables will be evaluated by the Shapiro-Wilk test.

The difference between the averages of the variables of emotional reaction and attention will be carried out by means of an analysis of variance (ANOVA) for dependent samples, taking into account the effect of drag. For these comparisons, the non-parametric tests of Kruskal Wallis and the Wilcoxon rank sum will be used, according to the number of levels of each factor.

For the results of the survey, in which the recall of the contents of the capsules will be evaluated after their screening, an analysis will be made to compare the difference in proportions between the groups with a good level of recall and those with a low level of recall for each category of educational level.

Statistical software Stata 13.1 will be used to analyze the data.

1. **Phase 6. Final production of the health capsules in maternal and neonatal safety**

Professional experts in the layout and development of audiovisual animation products will carry out the final production process, taking into account the changes suggested by the analysis of results of the neuromarketing strategy.

- - - 1. **Ethical considerations**

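### The protocol asks how effective the 12 capsules are, but hypothesis 1 covers one capsule at a time and states no overall capsules-versus-control estimate

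*Protocol*

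**What the plan says.** Research question 2 appears under Problem in the executive summary and again at the end of the Problem Statement: "What is the effectiveness of 12 knowledge capsules in maternal and neonatal health to achieve social appropriation of this knowledge in the target population". The overall objective under Objectives repeats the subject: "Design and evaluate the effectiveness of 12 knowledge capsules in maternal and neonatal health through a pilot study".

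In Phase 5, Statistic analysis, hypothesis 1 carries the plural heading "Comparison between capsules and video control". The null beneath it is singular, "H0: μ capsule X = μ video control", with a two-sided alternative, for average attention, emotional reaction and recall.

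The Phase 5 design paragraph exposes every subject to 12 capsules and one control clip, so that "each subject will have 13 evaluations". Under Process, the text adds: "The process of consolidating results will be done for each clip as shown in Figure 2". The content of that figure is not in the text available here.

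For attention and emotional reaction the planned method is "analysis of variance (ANOVA) for dependent samples, taking into account the effect of drag". Recall is analysed differently, as good against low recall by educational level, with no comparison between capsules and control.

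**The concern.** The question is put about 12 capsules and the hypothesis about one. Suppose that 5 of the 12 capsules differ from the control. The protocol does not say whether that makes the capsules effective, nor by how much they differ from the control overall. An overall statement would then have to rest on a count of significant capsules or on a contrast chosen after the results were seen.

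The design itself supports an overall contrast. The control is described as a video made without the evidence base and neuromarketing methods used for the capsules, so it differs from all 12 in the same respect. The sample-size text also refers to capsules, in the plural, against the control.

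**Working it through.** **The plan's own figure.** A one-way fixed-effects ANOVA with three groups, f = 0.3, alpha 0.05 and power 0.90 has noncentrality f²N = 0.09 × 144 = 12.96 on (2, 141) degrees of freedom. Power is 0.901, so 144 reproduces; at 150 it is 0.913. This is a comparison between three groups of subjects. It gives no information on the precision of any capsule-versus-control contrast, which is within subject.

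**Inputs for the contrasts.** n = 150 and 12 capsules plus one control per subject come from the protocol. A common SD of 1 and the correlations are assumptions, because the protocol gives none. Let ρc be the correlation between two capsules and ρx that between a capsule and the control. The 150 subjects are treated as one sample.

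**Formulas.**
- One capsule minus control: variance = 2(1 − ρx)/n.
- Mean of 12 capsules minus control: variance = [(1 + 11ρc)/12 + 1 − 2ρx]/n. With ρc = ρx = ρ this is (13/12)(1 − ρ)/n.

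Under equal correlation the variance ratio is (13/12)/2 = 13/24 = 0.542 and the SE ratio is √0.542 = 0.736, whatever ρ is.

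**At n = 150 and ρ = 0.5.** SE for one capsule = √(2 × 0.5/150) = 0.0816 SD. SE for the mean of 12 = √((13/12) × 0.5/150) = 0.0601 SD. Multiplying by 1.960 + 1.282 gives the difference detectable with 90% power: 0.265 and 0.195 SD. With ρ = 0.3 the pair is 0.313 and 0.230; with ρ = 0.7 it is 0.205 and 0.151.

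**Less favourable correlations.**

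| ρc | ρx | SE ratio |
|---|---|---|
| 0.5 | 0.3 | 0.82 |
| 0.7 | 0.4 | 0.88 |
| 0.8 | 0.5 | 0.90 |
| 0.9 | 0.5 | 0.95 |

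**Power if all 12 capsules share a shift of 0.20 SD (n = 150, ρ = 0.5).**
- Averaged contrast: 0.91.
- One capsule at 0.05: 0.69.
- One capsule at 0.05/12: 0.34.
- 13-level omnibus F, with noncentrality 150 × 0.20² × (12/13)/0.5 = 11.08 on (12, 1788) degrees of freedom: 0.55.

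**Power if only k capsules have the 0.20 SD effect and the rest have none.** The averaged difference is 0.20k/12.
- k = 5: 0.083/0.0601 = 1.39, and Φ(1.39 − 1.96) = 0.28. This is below the 0.69 for one effective capsule, and below its 0.34 at 0.05/12.
- k = 8: 0.133/0.0601 = 2.22, power 0.60.
- k = 9: 0.150/0.0601 = 2.50, power 0.70.

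The averaged contrast therefore overtakes an unadjusted test of one effective capsule when k/12 exceeds the SE ratio: 12 × 0.736 = 8.8, so k of at least 9. With an SE ratio of 0.82 the threshold is 10 (12 × 0.82 = 9.8), and with 0.95 it is all 12 (12 × 0.953 = 11.4).

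**The case against.** The strongest case on the other side is that the protocol is consistent if effectiveness is judged capsule by capsule. The capsules differ in content by phase and mode of delivery, results are consolidated per clip, the study is called a pilot, and Phase 6 uses the results to change capsules before final production. No go/no-go decision on the set is stated. This stands. A reader might infer that the capsules must be judged as one programme and that the trial cannot answer its question. The documents do not support that, because they never describe the target that way and the wording of the question admits both readings.

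It can also be said that the dependent-samples ANOVA treats all clips jointly, that a capsules-versus-control contrast is a routine follow-up, and that a statistical analysis plan, which is not shown, may define it. This stands in part. The absence can be asserted only of the protocol text. An omnibus F alone gives neither a direction nor an estimate, and it can reject because capsules differ among themselves.

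Thirdly, a reader might infer that the averaged contrast always has more power than a single-capsule test. The working shows that it does not. The gain needs an effect shared by most capsules, opposite effects would cancel, and the 0.736 ratio needs equal correlations. Capsules from one production process may well correlate more with each other than with the control.

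Finally, recall is the outcome named for the sample size, yet its planned analysis has no clip-level contrast. The averaged contrast does nothing for recall as that analysis now stands.

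**Conclusion.** The point holds as a clarification and a low-cost improvement. The protocol asks about 12 capsules, writes hypothesis 1 for one, and states neither an averaged contrast with the control nor how 12 results lead to one conclusion. It is not an internal contradiction.

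The averaged contrast is more precise than a single-capsule contrast in every correlation structure tried: 26% smaller SE under equal correlation, and roughly 5% to 18% smaller under the less favourable ones. These figures rest on assumed correlations and a common SD. The main reason to add the contrast is that it estimates the overall effect directly. Greater power is a conditional benefit.

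**What to change.** Under hypothesis 1 in Phase 5, Statistic analysis, add an overall hypothesis: the mean response over the 12 capsules equals the mean response to the control video. For attention and for emotional reaction, estimate it from each subject's mean over the 12 capsules minus the control value, and report a 95% confidence interval as the overall estimate. Keep the 12 capsule-specific contrasts and state that they guide the Phase 6 revisions. Extend the overall contrast to recall only if recall is scored per clip.

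If the sponsor intends effectiveness to be judged capsule by capsule only, the protocol should say so and state what pattern of results would support an overall claim.

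The cost is a few lines of text, with no extra subjects, measurements or visits. The drawback is that an average can hide a weak capsule or capsules with opposite effects, so it must be read together with the capsule-level results.

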**Analysis**

1. For the first phase of the project, corresponding to the RSL, a statistical combination of the results will be carried out independently, both for the randomized clinical trials and for cohort studies, through a meta-analysis, following an exploration of the presence of heterogeneity through the inconsistency test (I2) and the p-value of the chi-square test, and if there is variation in the definition of the evaluated outcomes. The statistical combination of the results will be made through meta-analysis of fixed effects, or in the case of heterogeneous data, a random effects model will be used. A sensitivity analysis will be carried out to study the influence of the risk of bias in the results of the meta-analysis.
2. For the neuromarketing strategy, corresponding to the final phase of the study, descriptive analysis of the data will be carried out. The normality of the variables will be evaluated by the Shapiro-Wilk test. The difference between the averages of the variables of emotional reaction and attention will be carried out by means of an analysis of variance (ANOVA) for dependent samples in case the variables are distributed normally, otherwise this difference will be analyzed by means of a Kruskal-Wallis test. For the analysis, statistics will be used for paired studies, taking into account that the subjects are part of the evaluation of all interventions.
3. For the results of the survey, in which the recall of the contents of the capsules will be evaluated, a proportional difference will be made between the groups with a good level of recall and those with a low level of recall for each category of educational level. The analysis of the collected data will be made using the statistical software STATA 12.0®.

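### For attention and emotional reaction, hypothesis 1 compares a capsule with the control video, but the only test named is a dependent-samples ANOVA with no capsule-control contrast attached to it

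*Protocol*

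**What the plan says.** The protocol's Phase 5 statistical analysis section lists four hypotheses. The first is headed "Comparison between capsules and video control", with the null "H0: μ capsule X = μ video control" and a two-sided alternative. The other three compare participant groups, levels of schooling, and people with and without children.

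For attention and emotional reaction, the same section says that the difference between averages "will be carried out by means of an analysis of variance (ANOVA) for dependent samples, taking into account the effect of drag" (I read drag as carry-over). It adds that "the non-parametric tests of Kruskal Wallis and the Wilcoxon rank sum will be used, according to the number of levels of each factor". The executive summary (Analysis, item 2) gives the same ANOVA for normally distributed variables; "otherwise this difference will be analyzed by means of a Kruskal-Wallis test". It justifies paired methods by "taking into account that the subjects are part of the evaluation of all interventions".

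The Phase 5 design has 12 capsules and one control clip, "so that each subject will have 13 evaluations". Recall is handled separately, as a comparison of proportions by educational level.

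Neither analysis section states which factor the dependent-samples ANOVA is applied to. Neither names a contrast or a reference level, or says how the ANOVA result answers hypothesis 1.

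**The concern.** Group, schooling and family history are between-subject factors. Clip is the only factor in the four hypotheses that is repeated within a subject, so it is the factor to which a dependent-samples ANOVA would naturally apply. With 13 levels, the null is that all 13 means are equal, and the control is one level among 13 with no special role.

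The 12 capsules cover different phases of childbirth and both routes of delivery, so some differences between them are likely. A significant F would show that at least one clip differs from another. It would not show which one, in what direction, or whether the capsules as a set differ from the control. The general aim is to evaluate the effectiveness of the capsules, and Phase 6 revises them on these results. The plan should therefore say which comparison carries that conclusion.

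**Working it through.** **The plan's own figure.** The sample size section uses a one-way fixed-effects ANOVA with three groups, f = 0.3, alpha 0.05 and power 0.90. With noncentrality N·f² on 2 and N − 3 df, N = 143 gives power 0.899 and N = 144 gives 144 × 0.09 = 12.96 and power 0.901. The stated 144 is reproduced. It is a between-subject calculation for three groups with its parameters chosen for recall, so it does not give the power of a within-subject capsule-control comparison of attention or emotional reaction.

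**Inputs for the check.** From the protocol: n = 150 subjects, k = 13 clips and alpha 0.05 (the sample size section's value). Assumed, because the protocol gives no variance or expected clip differences: compound symmetry, no carry-over, and differences d in units of the within-subject residual SD.

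**Formulas.**
- Overall F: df 12 and 149 × 12 = 1788; λ = n·Σ(μᵢ − μ̄)².
- Mean of 12 capsules minus control: df 1 and 1788; λ = n·(difference)²/(1 + 1/12).
- One capsule minus control: df 1 and 1788; λ = n·d²/2.
- Dunnett adjustment for 12 comparisons with a shared control: two-sided critical value 2.77.

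**Capsules differ, but their average equals the control.** Six capsules are at +d and six at −d.
- d = 0.10: λ = 150 × 12 × 0.01 = 18.0; F rejects 82%.
- d = 0.15: λ = 150 × 12 × 0.0225 = 40.5; F rejects 99.7%.
- The averaged contrast has λ = 0 in both cases and rejects 5%.

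**All capsules shifted from the control by the same d.** Here Σ(μᵢ − μ̄)² = d² × 12/13 and 1/(1 + 1/12) = 12/13. The F test and the averaged contrast therefore have the same λ, but the F test spreads it over 12 df.

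| d | λ (F and averaged contrast) | Overall F | Averaged contrast | One capsule, unadjusted | One given capsule, Dunnett |
|---|---|---|---|---|---|
| 0.20 | 150 × 0.04 × 12/13 = 5.54 | 27% | 65% | 41% | 15% |
| 0.30 | 150 × 0.09 × 12/13 = 12.46 | 62% | 94% | 74% | 43% |
| 0.40 | 150 × 0.16 × 12/13 = 22.15 | 90% | 99.7% | 93% | 76% |

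The shift detectable with 80% power is 0.355 for the overall F and 0.238 for the averaged contrast.

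**Multiplicity.** Under compound symmetry, the 12 capsule-control differences share the control and correlate 0.5. Testing each at 0.05 without adjustment gives a familywise error of about 0.32.

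**The case against.** A reader might infer that the protocol prescribes the wrong test outright: a 13-clip F test that rejects falsely when capsules merely differ from one another. The documents do not support that, for four reasons.

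1. **The 13-level test is an inference.** The ANOVA factor is not named. Hypothesis 1 is written for one capsule X, and the choice of non-parametric test depends on the number of factor levels, so two-level analyses are foreseen. A two-level dependent-samples ANOVA is the paired t-test, which would match hypothesis 1. The figures on clip-by-clip consolidation are not available, and the statistical analysis plan has not been seen. This stands in part: the pairwise reading is open, but no available text states it. The two-level test named, the rank sum, is for independent samples; it fits the children/no-children comparison rather than paired clips.

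2. **The rejections are not false in the global sense.** Saying that every capsule equals the control is the same as saying that all 13 clips are equal. If the capsules differ from each other, at least one differs from the control. This stands in full: the 82% is correct detection of some difference. It becomes an error only if read as a statement about the capsule average or about a particular capsule.

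3. **The power loss is not general.** It holds against the averaged contrast under a common shift. Against a Dunnett-adjusted test of one given capsule, the overall F is the more powerful (62% versus 43% at 0.30). This also stands.

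4. **No rule says that a significant F will be called effectiveness**, and in a pilot that feeds capsule revision, differences between capsules are themselves useful. That is fair. The plan also does not say which result would answer hypothesis 1.

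**Conclusion.** The point holds in a limited form. For attention and emotional reaction, the protocol fixes a capsule-control hypothesis and a test without connecting them. On the natural reading, the test is a valid global test that cannot answer the hypothesis for a given capsule or for the capsules on average. With 150 subjects it would reject about 82% of the time with capsules 0.10 within-subject SD either side of a control equal to their average. Under a common shift it has 27% power against 65% for the averaged contrast at 0.20, and 62% against 94% at 0.30.

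These figures rest on an assumed effect scale, compound symmetry and no carry-over. They apply only if the ANOVA is the 13-clip test. If pairwise capsule-control tests were intended, the gap is one of wording, and about 0.32 familywise error would apply if they were unadjusted. Nothing here concerns recall.

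**What to change.** In the Phase 5 statistical analysis section and in item 2 of the executive summary's Analysis section, state that for attention and emotional reaction:

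- Hypothesis 1 is tested from the within-subject model (subject random; clip and viewing position fixed) by the planned contrast of the mean of the 12 capsules minus the control.
- The 12 capsule-minus-control comparisons follow, with Dunnett-type adjustment.
- A significant overall F test across clips is not, on its own, read as capsule effectiveness.

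The data collected and the sample size are unchanged, and all the contrasts come from one fitted model. The cost is lower power for single-capsule claims: with adjustment, about 43% for a given capsule at a shift of 0.30 within-subject SD, against 74% unadjusted.
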